#### Data sources and measures

##### Effectiveness/reach

Effectiveness will be examined by calculating how many patients were eligible (positive AUDIT-C) based on EHR data and the proportion who enrolled in the intervention as collected by the text platform. Demographics will also be collected from the EHR and text platform to examine differences in characteristics between who was eligible based on AUDIT-C score and who enrolled. In the text platform, each study site will have a unique enrollment text code number, allowing for tracking of patients that enrolled by site and when they enrolled, demographics, and responses to the intervention tailoring questions (e.g., drinking patterns, self-efficacy, motivation). We anticipate there will be ~5000 UAU eligible patients identified during the study trial period based on (1) sites’ current census, (2) current screen positive rates, and (3) screening completion rates based on our previous evaluations in this integrated health system.

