#### Analysis

The same procedures described in aim 1 will be used to analyze qualitative data for aim 3. For the reach/effectiveness quantitative data, we will calculate a proportion for each study condition (e.g., numerator: # of patients in control or intervention sites who enrolled in the intervention; denominator: # of patients with positive AUDIT-C) and use *z*-tests for independent proportions [93] to examine whether control and intervention sites differ significantly. We will also use *z*-tests to examine differences in demographics between those eligible and enrolled to determine whether there are gender or racial disparities. For these proportional analyses [94], to achieve 80% power, a sample size of at least 300 in each condition is needed (total of 600) to detect a 10% difference in proportions with significance level of *p* = .05. For the feasibility/acceptability staff and patient survey data, we will calculate descriptive statistics for each. We will triangulate this quantitative data with the qualitative data by merging the results. No identifying information will be maintained by the study team for any staff or patients; all participants will be identified with a participant ID.

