The focus of this study is primarily on studying implementation outcomes, and not patient outcomes; therefore, we will not randomize patients to the text-messaging intervention; instead, all patients will receive the intervention. However, we will collect valuable data from patients to assess feasibility and acceptability of the intervention from their perspective; determine the proportion who engage with the intervention in a real-world situation; examine disparities in gender, race, and ethnicity in enrolled vs. not; and understand why patients enrolled. All of the more than 150 hospitals in New York State are now required by state regulation to screen for substance misuse and such policies are being implemented elsewhere [96]; therefore, findings have the potential to be applied state- and nation-wide and a large number of sites would be available for a larger study.

This project moves forward the implementation science on technology interventions, a fairly new area of research. While the technology focus of this project is on text messaging, findings may be broadly applicable to patient-facing mHealth technologies. Text-messaging interventions have the potential to reach as many patients impacted by UAU as possible, including those traditionally underserved, in a scalable, low-burden manner; this study will illuminate strategies to reach that potential.

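### The two-proportion z-tests assigned to racial disparities do not fit a race variable with more than two categories, and the Analysis section and Discussion disagree on ethnicity and on the groups compared

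*Protocol article*

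**What the plan says.** The question of who enrols appears in three places in the protocol article.

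- **Methods, Aim 3, Effectiveness/reach:** demographics are collected "to examine differences in characteristics between who was eligible based on AUDIT-C score and who enrolled".
- **Methods, Aim 3, Analysis:** "We will also use *z*-tests to examine differences in demographics between those eligible and enrolled", with the purpose given as "to determine whether there are gender or racial disparities". The sentence before it names the test used for the two arms: "use *z*-tests for independent proportions [93] to examine whether control and intervention sites differ significantly". The sentence after it covers the proportional analyses together, "with significance level of *p* = .05".
- **Discussion:** the study will "examine disparities in gender, race, and ethnicity in enrolled vs. not".

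The article lists no race categories, names no overall test for race and does not say that race will be reduced to two groups.

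**The concern.** Three things do not fit together.

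1. **Test and variable.** A two-proportion z-test compares the share with a single yes/no characteristic in two groups. Race with more than two categories cannot be tested that way in one step. Either each category gets its own test, and nothing says how several p-values become one conclusion, or race is collapsed to two groups, which can hide differences among those merged.
2. **Characteristics.** The Discussion lists gender, race and ethnicity. The sentence that assigns the test gives gender and race as its purpose.
3. **Groups.** The Analysis and Effectiveness/reach sections set eligible patients against enrolled patients, who are meant to be a subset of the eligible. The Discussion sets enrolled against not enrolled. A z-test for independent proportions suits the second pair but not the first.

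At stake is whether a reported disparity, or its absence, can be read at the stated significance level. The Background and Discussion both argue for texting partly on its potential to reach underserved patients.

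**Working it through.** **The plan's own figure.** The Analysis section gives 300 per condition for 80% power "to detect a 10% difference in proportions" at .05. The baseline proportion and sidedness are not stated. With the pooled-variance formula

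n = [z(.975)·√(2p̄(1−p̄)) + z(.80)·√(p1(1−p1) + p2(1−p2))]² / (p1−p2)²,

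an assumed 20% vs 30%, two-sided, gives (1.96·√0.375 + 0.8416·√0.37)² / 0.01, or 294 per group after rounding up. The stated 300 is therefore consistent with a baseline near 20%. That baseline is an assumption, and nothing below depends on it.

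**Inputs for the disparity tests**

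- Eligible patients: about 5000 (Effectiveness/reach).
- Level: .05 (Analysis), taken as two-sided, so |z| > 1.96.
- Enrolled fraction f: not stated for this trial. The Background cites 44% acceptance in one ED study. Range used: 2% to 44%.
- Race mixes, assumed: 60/25/15; 50/20/20/10; 45/20/15/12/8; 45/20/15/10/7/3 (percent).
- No true disparity, independent patients, 40,000 simulated samples per setting.

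**Enrolled vs not enrolled (the Discussion's groups).** The chance that at least one of k unadjusted category tests is significant would be 1 − 0.95^k if the tests were independent. They are not, because the shares sum to one, so the simulated values are somewhat lower.

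| Race categories | 1 − 0.95^k | Simulated, over all f | One overall chi-square, k−1 df |
|---|---|---|---|
| 3 | 14.3% | 11.8–12.2% | about 5% |
| 4 | 18.5% | 16.5–17.0% | about 5% |
| 5 | 22.6% | 20.6–21.3% | about 5% |
| 6 | 26.5% | 23.6–25.2% | about 5% |

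**Eligible vs enrolled (the Analysis section's groups).** Let N be the number eligible, fN the number enrolled, and p the share in one category. The enrolled-minus-eligible difference equals (1−f) times the enrolled-minus-not-enrolled difference.

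- True variance: (1−f)²·p(1−p)·[1/(fN) + 1/((1−f)N)] = p(1−p)(1−f)/(fN)
- Variance the independent-samples test assumes: p(1−p)·[1/(fN) + 1/N] = p(1−p)(1+f)/(fN)
- Ratio, true to assumed: (1−f)/(1+f)

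The real error of one nominal 5% test is therefore 2·[1 − Φ(1.96·√((1+f)/(1−f)))]. At f = 0.20 this is 2·[1 − Φ(1.96 × 1.225)] = 2·[1 − Φ(2.40)] = 1.6%.

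| Reach f | Error per test | At least one of k race tests, simulated (k = 3 to 6) |
|---|---|---|
| 2% | 4.6% | 10.8–21.6% |
| 10% | 3.0% | 7.5–15.8% |
| 20% | 1.6% | 4.3–9.1% |
| 30% | 0.8% | 2.0–4.4% |
| 44% | 0.17% | 0.5–1.0% |

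Two errors pull in opposite directions: repeated testing raises the false-positive rate and the ignored overlap lowers it. The overlap also makes the single gender test conservative, with the error in the middle column.

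**The case against.** The strongest reply is that this is a condensed article on a pilot. Race categories, an overall test and handling of multiplicity for a secondary analysis are commonly left to the full protocol or analysis plan, and race could be dichotomised there. That stands as far as omissions go, and category-by-category testing is an inference rather than something the article states. It does not remove the point that the article names a test unsuited to a multi-category characteristic, nor the mismatch between its own sections.

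Two stronger readings are tempting, and the documents support neither.

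- **A reader might infer that chance racial disparities will be over-called.** That is assured only if race is tested by category in enrolled vs not-enrolled patients. With the groups as the Analysis section words them, the direction depends on reach, which the article does not state, and from about 30% reach the tests under-call.
- **A reader might infer that ethnic disparities will go untested.** The Discussion commits to examining them, and the Analysis section applies its z-tests to demographics in general before naming gender and race. What is missing is an explicit assignment of the test to ethnicity.

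One could add that separate tests for race, gender and ethnicity still carry about 14% across the three if independent (1 − 0.95³ = 14.3%). That is true. They answer three separate questions, each then held at 5%, and the point here does not rest on adding across characteristics.

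**Conclusion.** The concern holds in a limited form. The named test cannot judge a race variable with more than two categories in one step, and the Analysis section and Discussion differ both on ethnicity and on the comparison groups. If race is tested by category, the chance of at least one false racial disparity is about 12% to 25% for 3 to 6 categories in enrolled vs not-enrolled patients. In eligible vs enrolled patients it ranges from 21.6% (six categories, 2% reach) to 0.5% (three categories, 44% reach). Neither version is held at 5%. These figures rest on assumed race mixes, about 5000 eligible and independent patients, two-sided testing, and every enrolled patient being among the eligible.

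The priority is minor. The pilot's main goals, and the criteria for moving to a larger trial, are feasibility, acceptability and reach. No progression decision is tied to the disparity tests.

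**What to change.** In the Analysis section of Aim 3:

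1. Define the comparison as enrolled vs not-enrolled eligible patients, matching the Discussion, if text-platform and EHR records can be linked. The overall test needs this too: a chi-square on eligible vs enrolled would have the same non-independence. If linkage is not possible, label the comparison descriptive.
2. Use one chi-square or likelihood-ratio test on k−1 degrees of freedom for race, and one test each for gender and ethnicity, so that the list agrees with the Discussion.
3. Report the enrolment proportion in each category with a 95% confidence interval as description, not as further tests.

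The cost is a sentence or two, one extra test and the linkage step. The downside is that a difference confined to one small race category is less likely to reach significance. The category-specific intervals would still show it.

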Reviews of text-messaging interventions for health behaviors broadly have found that the majority were effective and that there is strong evidence to support the value of integrating them into public health practice [18, 23, 24]. Text interventions are an acceptable and feasible strategy to enhance the delivery of care for persons with substance use problems [17, 25–27]. A recent meta-analysis found that text-messaging alcohol interventions reduce alcohol consumption compared with no or basic health information [28]. For example, people with harmful drinking patterns significantly reduced drinking frequency and quantity after receiving daily texts [29]. Patients with alcohol use disorder perceive that text interventions may help them remain abstinent [30]. The benefits of harnessing text interventions for UAU in the ED could be considerable because they are low burden for patients and acceptable and effective [31]. For example, discharged trauma center patients who received a text intervention reduced hazardous drinking as compared to usual care controls [32] and the majority of trauma patients would enroll if offered a text intervention [33]. Among patients recruited from EDs, text interventions for UAU are effective in supporting them in meeting drinking goals and making drinking reductions, including reductions in binge drinking and number of drinks consumed per day [34, 35]. Furthermore, 44% of ED patients accepted a text intervention and those who accepted had higher rates of treatment attendance after discharge from the ED as compared to those who did not accept [9]. These studies show broad efficacy for text interventions in EDs with potential to reach diverse populations; however, no studies have developed and tested a strategy for systematically offering them to patients in EDs in a scalable manner.

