Aim 2: use a stakeholder-engaged intervention mapping process to develop a multi-component implementation strategy for EDs

Aim 3: conduct a mixed method 2-arm cluster randomized pilot study in 4 EDs that serve ~11,000 UAU patients per year to assess the feasibility, acceptability, and preliminary effectiveness of the implementation strategy

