### Aim 3: Examine the feasibility, acceptability, and preliminary effectiveness of the implementation strategy

#### Design

In line with recommendations pertaining to the scope and target outcomes of pilot studies for implementation trials [83–85], the main goal of this pilot trial is to assess the (1) feasibility (i.e., perceptions among ED clinical staff members that the implementation strategy can be successfully used), (2) acceptability (i.e., perceptions among ED clinical staff members that the implementation strategy is agreeable, palatable, or satisfactory), and (3) and preliminary effectiveness of the implementation strategy. We will operationalize our effectiveness outcome as “reach” (i.e., proportion of eligible patients that enroll in the text intervention), which is a key outcome recommended in the implementation science literature [83, 85–87]. The design is a mixed method, two-armed, study in 4 EDs (2 assigned to the new implementation strategy vs. 2 implementation as usual control). Qualitative and quantitative measures will be collected and analyzed simultaneously and merged—qualitative data will provide context to and explanation of the quantitative results in a complimentary way, representing a QUAL + QUAN structure that gives equal emphasis to both types of data [65].

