#### Study site randomization

The study will be conducted within a large integrated health system in the Northeast of the USA. Because the number of study sites for this pilot is relatively small, simple unrestricted randomization may not be sufficient to ensure balance between study conditions. Pairing of EDs would improve balance but may reduce study power and is not recommended for small numbers of clusters [88]. Therefore, we will use a minimization procedure to ensure overall balance on three important covariates: annual ED census, location (urban/suburban), and AUDIT-C positive rate. A computerized algorithm will be used to identify all possible allocations that meet the balancing constraints and one of the allocations will be randomly selected [89]. A data analyst not associated with the study will conduct this procedure to minimize bias. Study sites and data analysts will be blinded to the study condition.

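### The 80% power claimed for reach with 300 patients per condition ignores that four EDs, two per arm, are randomised

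*Protocol article*

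**What the plan says.** The third aim (Background) is to "conduct a mixed method 2-arm cluster randomized pilot study in 4 EDs". The Aim 3 Design section gives the split: "2 assigned to the new implementation strategy vs. 2 implementation as usual control". The section on study site randomization recognises the small number of units ("Because the number of study sites for this pilot is relatively small") and uses constrained allocation to balance the arms.

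The Analysis section of Aim 3 then pools patients within each condition, divides enrolled by AUDIT-C-positive patients, and applies z-"tests for independent proportions". The stated purpose of these tests is "to examine whether control and intervention sites differ significantly". The power statement follows: "to achieve 80% power, a sample size of at least 300 in each condition is needed (total of 600) to detect a 10% difference". Alpha is set at 0.05. No base rate, sidedness, ICC or design effect is given. Under Data sources and measures, about 5,000 eligible patients are expected over the trial period.

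**The concern.** The implementation strategy is given to an ED and acts through that ED's workflow, so patients of one ED share its staff, screening practice and way of offering the programme. Their enrolment outcomes are therefore likely to be correlated. A patient-level z-test and its power calculation assume no such correlation. The number of EDs, not of patients, then limits what can be learned about the difference between arms.

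Two things are at stake. First, a minimum of 600 against about 5,000 expected patients looks like a wide margin, although more patients per ED cannot make up for having two EDs per arm. Second, the Discussion makes preliminary effectiveness one of the inputs to the decision on a larger trial. A significant z-test could reflect ordinary differences between EDs, and a valid test could miss a real 10-point gain.

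**Working it through.** **Inputs.** From the article: 300 per condition, 80% power, a 10-point difference, alpha 0.05, two EDs per arm, about 5,000 eligible patients. Assumed: two-sided test (the text asks whether the sites differ); equal EDs, so m = 300/2 = 150 or 5,000/4 = 1,250 patients per ED; base rate 20% vs 30%; ICC 0.001 to 0.05, because no ICC is given.

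**Step 1: reproduce the stated figure.** For equal groups with pooled variance:

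n = [1.96·√(2·p̄·(1−p̄)) + 0.8416·√(p₁(1−p₁) + p₂(1−p₂))]² / (p₂−p₁)²

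For 20% vs 30%, p̄ = 0.25:

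n = [1.96·√0.375 + 0.8416·√0.37]² / 0.01 = (1.2002 + 0.5119)² / 0.01 = 293.2, so 294 per group.

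Power at 300 is 80.9%. The figure is thus reproduced by a calculation with no allowance for clustering.

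**Step 2: effective sample size.** The design effect is DE = 1 + (m−1)·ICC, and the effective n per arm is 2m/DE. As m grows this tends to 2/ICC. It stays below 300 whenever ICC > 2/300 = 0.0067. Example at ICC 0.01 with m = 1,250: DE = 1 + 1,249·0.01 = 13.49, and effective n = 2,500/13.49 = 185.

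**Step 3: power of a valid test.** Comparing two ED proportions with two leaves 2 + 2 − 2 = 2 degrees of freedom and a critical value of 4.303. The noncentrality is 0.10/√(0.37/n_eff), with 0.37 = 0.2·0.8 + 0.3·0.7.

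| ICC (assumed) | m per ED | DE | n_eff per arm | Noncentrality | Power, 2-df t |
|---|---|---|---|---|---|
| 0.001 | 150 | 1.15 | 261 | 2.66 | 33% |
| 0.01 | 150 | 2.49 | 120 | 1.80 | 19% |
| 0.05 | 150 | 8.45 | 35.5 | 0.98 | 9% |
| 0.001 | 1,250 | 2.25 | 1,112 | 5.48 | 78% |
| 0.01 | 1,250 | 13.49 | 185 | 2.24 | 26% |
| 0.02 | 1,250 | 25.98 | 96 | 1.61 | 16% |
| 0.05 | 1,250 | 63.45 | 39.4 | 1.03 | 10% |

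Beta-binomial simulation (200,000 runs per row) agrees to within about one percentage point, giving 10% in the third row and 17% in the sixth.

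The few degrees of freedom matter on their own. At ICC 0 with 300 per arm the noncentrality is 0.10/√(0.37/300) = 2.85, and 2-df power is 36%. If the normal reference is kept and only the design effect applied, power with 300 per arm is 75%, 43% and 16% at ICC 0.001, 0.01 and 0.05.

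**Step 4: type I error of the planned z-test.** Ignoring DE understates the standard error by √DE, so the actual error is 2·[1 − Φ(1.96/√DE)]. At ICC 0.01:

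- m = 150: 1.96/√2.49 = 1.24, giving about 21%.
- m = 1,250: 1.96/√13.49 = 0.53, giving about 59%.

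Simulation at 20% reach gives the same figures. More patients make the planned test less valid.

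**Step 5: achievable precision.** With 20% reach in both arms and m = 1,250, the 95% half-width for the difference is 4.303·√(2·0.2·0.8/n_eff):

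- ICC 0.01: 4.303·√(0.32/185.3) = 0.179, about ±18 points
- ICC 0.02: 4.303·√(0.32/96.2) = 0.248, about ±25 points
- ICC 0.05: 4.303·√(0.32/39.4) = 0.388, about ±39 points

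**Step 6: base rate (minor).** Ignoring clustering, two-sided, the requirement per equal group is 199 for 10% vs 20%, 250 for 15% vs 25%, 294 for 20% vs 30%, 356 for 30% vs 40% and 392 for 44% vs 54%. By symmetry, 300 is enough again from about 70% vs 80%.

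**The case against.** The strongest defence is that this is a pilot. The article calls effectiveness preliminary and defers the fully powered test to a later trial. Its progression criteria combine effectiveness with feasibility and acceptability, and nothing ties progression to a significant z-test. No site or patient number was set by the 300. This tempers the consequence, and it would be conjecture to say that the progression decision will rest on this test. It does not rescue the statement: a pilot need not claim 80% power, and this one does, for a test that its own design does not support.

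A second objection is that the ICC is unknown. That stands, and the results vary widely with it. With all 5,000 patients and ICC 0.001, 2-df power is 78% at 20% vs 30% and about 89% at 10% vs 20%. The 300 per condition as stated does not share that protection: on 2 degrees of freedom at 20% vs 30%, even ICC 0 gives only 36%.

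A reader might also infer more than the article supports:

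- **That 300 works only at 20% vs 30%.** It does not follow. That pair is about the upper end of the low range in which 300 suffices. Lower base rates need fewer patients, and a one-sided reading, which the text does not exclude, fits control rates of about 34% to 45%.
- **That the comparison fails because "44% of ED patients accepted a text intervention".** This is acceptance in a cited study, not a design assumption. Reach here is enrolment among all AUDIT-C-positive patients. Even at that rate, about 2,500 per arm would give more than 99.9% power if clustering were ignored, so the base rate is moot for reach.
- **That the disparity tests need about 390 per group.** That figure assumes two equal groups. The plan compares eligible with enrolled patients, which is neither an equal split nor a between-arm comparison.

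**Conclusion.** Wrong as written: the stated property is not delivered, because the calculation is for a design that the trial does not use. The fault is a design assumption, not arithmetic, since 300 reproduces at about 20% vs 30%.

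The size depends on assumed ICCs, equal EDs and the 20% vs 30% example. Under these, a valid ED-level test with 300 per arm has roughly 10% to 33% power, and seeing all the expected patients brings it to 80% at none of the ICCs examined. The planned z-test has an inflated false-positive rate at any positive ICC, and the inflation grows with patients per ED. The missing base rate and sidedness leave the 300 hard to check, but for reach they are secondary.

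**What to change.** In Methods, Aim 3, Analysis:

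1. Withdraw the 80% power claim for the between-arm reach comparison.
2. State that two EDs per arm cannot support a powered between-arm test.
3. Report reach for each ED, and the difference between arms with an ED-level interval in place of the unadjusted z-test. Give the expected precision over a stated ICC range, for example the half-widths in Step 5, labelled as resting on assumed ICCs, 20% reach and about 1,250 patients per ED.
4. If 300 is kept for any patient-level comparison, state its base rate and sidedness. Two-sided with equal groups, it suffices up to about 20% vs 30% and from about 70% vs 80%, and falls short in between.

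The cost is a less favourable stated figure and a few rewritten sentences. No extra patients or sites are needed.
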